## Abstract

**Introduction:**

Depression, cardiovascular diseases and diabetes are among the major non-communicable diseases, leading to significant disability and mortality worldwide. These diseases may share environmental and genetic determinants associated with multimorbid patterns. Stressful early-life events are among the primary factors associated with the development of mental and physical diseases. However, possible causative mechanisms linking early life stress (ELS) with psycho-cardio-metabolic (PCM) multi-morbidity are not well understood. This prevents a full understanding of causal pathways towards the shared risk of these diseases and the development of coordinated preventive and therapeutic interventions.

**Methods and analysis:**

This paper describes the study protocol for EarlyCause, a large-scale and inter-disciplinary research project funded by the European Union’s Horizon 2020 research and innovation programme. The project takes advantage of human longitudinal birth cohort data, animal studies and cellular models to test the hypothesis of shared mechanisms and molecular pathways by which ELS shapes an individual’s physical and mental health in adulthood. The study will research in detail how ELS converts into biological signals embedded simultaneously or sequentially in the brain, the cardiovascular and metabolic systems. The research will mainly focus on four biological processes including possible alterations of the epigenome, neuroendocrine system, inflammatome, and the gut microbiome. Life-course models will integrate the role of modifying factors as sex, socioeconomics, and lifestyle with the goal to better identify groups at risk as well as inform promising strategies to reverse the possible mechanisms and/or reduce the impact of ELS on multi-morbidity development in high-risk individuals. These strategies will help better manage the impact of multi-morbidity on human health and the associated risk.

## 1. Introduction

### 1.1 Early life stress and psycho-cardio-metabolic multi-morbidity

The World Health Organisation has identified mental disorders, including depression, cardiovascular diseases and diabetes among the six major non-communicable diseases [1]. Individually, each of these groups of diseases represents a burden at the individual and population level. Depression alone is the single largest contributor to global disability, accounting for 12% of total years lived with disability [2] with more than 300 million individuals affected per year. Cardiovascular diseases (CVDs) remain the prime cause of mortality worldwide, accounting for about a third of annual deaths [3]. Finally, type 2 diabetes and related metabolic dysfunctions, including obesity, are a major public health challenge, with an average prevalence of over 8% in the general population [4]. In addition to their separate complexity, existing research has shown important multi-morbidity between these diseases, where multi-morbidity is defined as the co-occurrence of two or more chronic conditions [5]. Epidemiological studies have indeed shown that for example patients experiencing depression are more likely to have comorbid CVD [6], type 2 diabetes [7], or both [8]. However, the specific causative mechanisms leading to psycho-cardio-metabolic (PCM) multi-morbidity are not well understood, which limits the development of effective preventive and therapeutic measures.

Recent evidence suggests that many mental and physical conditions find their origins in exposure to stress early in life, otherwise defined as early-life-stress (ELS) [9]. ELS can be both prenatal, such as exposure to clinically-significant depression *in utero*, and postnatal, such as emotional, physical and sexual abuse or neglect in childhood, parental psychopathology and separation, prepubertal bullying, as well as victimisation or violence by peers [10]. Growing evidence has supported an association between ELS (both prenatal and postnatal) and the development of the PCM conditions. Specifically, patients with a history of ELS have higher vulnerability for depression [11], and higher risk of developing cardiovascular disease [12], obesity [13] and type 2 diabetes [14] later in life. Prenatally, the overarching hypothesis is that the maternal stress response is passed to the fetus, via stress hormones crossing the placenta, which affects subsequent brain and physical development of the fetus and newborn [15]. During childhood, exposure to excessive levels of stress early in life can cause several biological alterations which can ultimately favour the development of PCM multi-morbidity [16]. As suggested by Barker’s work on the developmental origins of chronic diseases, including PCM conditions [17], the exact predictors of the development of these diseases are to be linked with variations of key systems during the developmental stage. Examples of key biological system alterations due to responses to stress include hypothalamic-pituitary-adrenal (HPA) axis changes as a response to stress [18], changes in the inflammatory response [19], microbiome dysbiosis [20,21] and overall bio-psycho-social axis dysfunction [22]. While ELS has also been linked to resilience in adulthood [23], our research will focus on understanding the mechanisms leading to the negative consequences, in particular PCM multi-morbidity. Considering that the prevalence of ELS, both *in utero* and postnatally, whether mild or severe, has reached alarming heights [15], this area of research is essential for future disease prevention and health promotion.

The objective of this paper is to present the EarlyCause project, a large-scale interdisciplinary research that aims to infer evidence for causative mechanisms linking pre- and postnatal ELS to PCM multi-morbidity, even decades after the exposure itself has ceased. To explain this enduring effect, EarlyCause will seek to identify both biological mediators and environmental moderators. With regards to biological mediators, the hypothesis is that the enduring effects of ELS may reflect in part a “biologically embedding”, whereby ELS alters biological development and function in a way that engenders latent vulnerability for poor health outcomes and increased susceptibility. This is supported by the identification of numerous biological correlates of ELS, and previously mentioned, including neuroendocrine dysregulation, heightened inflammatory response, changes in gut microbiota composition, and, more recently, alterations to the epigenome. The ambition of EarlyCause is to go well beyond reductionist approaches which have traditionally investigated new biomedical knowledge while treating disease classes, biological scales and temporal domains (*e*.*g*. childhood vs. adulthood) separately. We will thus investigate more holistic models of the causative pathways by building on the experience of our consortium in advanced methods such as Mendelian randomisation, structural equation modelling, multi-omics, and machine/deep learning. We will detail below EarlyCause objectives and hypotheses, as well as the methods that will be implemented to test these hypotheses (see Method section).

Furthermore, the EarlyCause consortium fully understands that given the prevalence of ELS affecting millions of mothers and children, important efforts need to be dedicated from day one to maximising the clinical and socioeconomic impacts. As one of its core objectives, EarlyCause will ensure that each impact is adequately assessed from clinical and non-clinical perspectives, as to allow future exploitation of the innovation outputs. This work will be done while taking into account the current gaps and limitations due to the single-disease frameworks that have dominated for a very long-time research, biotech innovation and healthcare.

### 1.2 Rationale and overview of the EarlyCause project

EarlyCause is the product of a collaboration between 14 participating institutions across Europe (Table 1) and is supported by the European Union’s Horizon 2020 research and innovation programme (SC1-BHC-01-2019).

**Table 1 pone.0245475.t001:** Participating institutions in the EarlyCause project.

Participant no.	Participant organisation name	Acronym	Country
1 (Coordinator)	Universitat de Barcelona	UB	ES
2	European Molecular Biology Laboratory	EMBL	DE
3	Erasmus Medical Centre Rotterdam	EMC	NL
4	University of Zurich	UZH	CH
5	King’s College London	KCL	UK
6	Consejo Superior de Investigaciones Cientificas	CSIC	ES
7	Centre Européen de Recherche en Biologie et Médicine	CERBM	FR
8	University of Oulu	OULU	FI
9	Fatebenefratelli Institute	IRCCS	IT
10	University of Bath	UOB	UK
11	VU Medical Centre, Amsterdam	VUMC	NL
12	Empirica Communication and Technology Research	EMP	DE
13	Combinostics Oy	COMBI	FI
14	Universitat Pompeu Fabra	UPF	ES

EarlyCause will investigate the hypothesis that ELS, as a risk factor for depressive, cardiovascular and metabolic disorders individually, is a cause of multi-morbidity between these conditions. From a biological point of view, the main hypothesis is that ELS activates a chain of events leading to cellular, molecular, epigenetic and microbial changes from the norm. This causative chain would ultimately trigger specific cellular and tissue phenotypes and comorbid pathological traits in the mental, cardiovascular and metabolic domains.

To this end, EarlyCause’s overarching concept is to build upon a unique repertoire of longitudinal data in humans across the lifespan and conduct mechanistic studies in established animal and cellular models to:

Identify the causal mechanisms linking exposure to ELS to the risk of multi-morbid symptoms across life;Delineate the potential molecular mechanisms underlying these causal associations;Discover new biomarkers tapping into multiple biological domains;Build integrative computational models and proof-of-concept tools for multi-morbidity assessment.

The project will focus on four candidate families of biological pathways that have been linked to ELS, specifically:

**Epigenetic alterations** are a presumed link between stress exposure and phenotypes. Clear associations between early-life adverse exposure and epigenetic processes (e.g. DNA methylation) and between these epigenetic modifications and later health outcomes have been shown both in humans [24–26] and mouse models [27].**HPA changes** have been associated with ELS exposure [18]. Molecular components of the HPA axis provide a relay chain across the body from the brain to the periphery, and some of the final products (glucocorticoid hormones) are potent regulators of glucose and lipid metabolism. Thus, this represents a central candidate mechanistic player in the aetiology of multi-morbid symptoms.**Inflammatory pathways** are a form of cellular response to ELS [19] reflecting activation of white blood cells in the circulation and peripheral tissues such as the spleen, lymph nodes and adipose tissue. Inflammatory components may have profound effects on the cardiovascular system, endothelial accumulation and activation of plaques, and adipose tissue metabolism, whose dysfunction has been associated with stress-related diseases including depression, cardiovascular disease and diabetes.**Gut microbiome** is a major contributor to health and disease [20,21], which plays a key role in modulating immune, neuroendocrine and behavioural responses to ELS, as proven mainly in mouse models [28].

In addition to these biological factors, EarlyCause will test the potential moderating role of key factors such as sex, socioeconomics, and lifestyle in the association between ELS and multi-morbidity development. Evidence for causality, mediation and moderation will be used to identify potential targets for intervention acting on the causative mechanisms to reduce the impact of ELS on multi-morbidity development in high-risk individuals.

Specifically, using longitudinal human data, as well as animal and cellular models we aim to address the following hypotheses (Table 2).

**Table 2 pone.0245475.t002:** Table of hypotheses for longitudinal human data, animal and cellular models.

Model	Hypotheses
Longitudinal human data (section 2.1)	Hypothesis 1: Early-life stress, including sexual, physical, psychological abuse and/or neglect in early life, is a causal factor in the development of PCM multi-morbidity. Specifically, ELS is a shared risk factor for pre-clinical psychological and cardiometabolic symptoms in childhood and PCM multi-morbidity in adulthood;
	Hypothesis 2: Specific alterations in DNA methylation inflammation, neuroendocrine function, and/or the gut microbiota mediate the ELS effects on PCM multi-morbidity;
	Hypothesis 3: The association between ELS and PCM is modifiable by lifestyle factors. We hypothesise positive moderation (prevention) by physical activity, dietary factors and sleep. In contrast, we hypothesise that the association is exacerbated by smoking and alcohol consumption;
	Hypothesis 4: PCM multi-morbidity is partly heritable and the individual genetic determinants of depression, and cardiometabolic diseases form a joint genetic factor of PCM symptoms in child- and adulthood.
Animal model (section 2.2)	Hypothesis 1: Exposure to pre- and postnatal stress induces behavioural, cardiovascular and metabolic changes across adulthood in mice;
	Hypothesis 2: The effect of pre- and postnatal stress on the above outcomes (Hypothesis 1) is mediated by similar epigenetic and molecular changes associated with PCM multi-morbidity symptoms previously identified in the human model.
Cellular model (section 2.3)	Hypothesis 1: Exposure of cells from the brain and peripheral organs to stress-related insults (cortisol and cytokines) induces cellular changes relevant to PCM multi-morbidity;
	Hypothesis 2: Mechanisms underlying the effect of the stress-related insults on the aforementioned cell types (Hypothesis 1) are mediated by molecular and gene expression changes previously identified both in the human and animal models.

## 2. Methods

EarlyCause’s methodology is divided into multiple steps. As shown in *Fig 1*, the study protocol aims to triangulate evidence based on (1) longitudinal human data, (2) animal and cellular models, as well as (3) computational bioinformatics and machine learning methods. Concretely, hypotheses on associations between ELS and PCM outcomes, as well as on potential biological mediators and modifiers, will be generated from the longitudinal human data, and then translated into experimental designs to be validated in the animal and cellular models, which will be leveraged to identify the relevant causative mechanisms and molecular pathways (implementation details are provided in Sections 2.1 & 2.2).

**Fig 1 pone.0245475.g001:**
[figure not shown]
Schematic overview of the EarlyCause project, that will study the link between ELS (1) and multi-morbidity (3), as mediated by biological pathways (2). Large-scale life course human data (4), as well as experimental and computational models, will be used to identify and validate the causative mechanisms.

EarlyCause will implement a ‘triangulation’ approach, which will capitalise on the complementary strengths of epidemiological and genetic methods in humans, experimental animal and cellular models, and *in silico* data integration pipelines, as shown in *Fig 2*. This will enable us to iteratively and dynamically:

Apply association analyses and latent modelling to large-scale longitudinal human data on ELS, resulting in the identification of potential new candidate biomarkers of PCM multi-morbidity, as well as novel hypotheses on underlying causative mechanisms;Apply causal inference methods, including structural equation modelling, Mendelian randomisation, and molecular mediation, to infer the causal relationships between ELS, biological mediators and the multimorbid outcomes;Validate the mechanisms and identify the associated molecular pathways in pre- and postnatal animal models, using established cellular models of stress;Integrate the identified determinants and molecular markers of ELS into computational models of multi-morbidity across the life span, and design a proof-of-concept decision support tool for PCM multi-morbidity risk assessment, by extending an existing single-disease e-health tool commercialised by EarlyCause partner COMBI (*i*.*e*., from the DSF^®^: *Disease State Fingerprint [29,30]* to the MSF: *Multi-morbidity State Fingerprint*).

**Fig 2 pone.0245475.g002:**
[figure not shown]
Overall methodology of the EarlyCause project, including (A) research platform of harmonised data from existing resources, research protocols and best practices; (B) triangulation approach, which will capitalise on the complementary strengths of epidemiological and genetic methods in humans, experimental animal and cellular models, and in silico data integration pipelines; and (C) expected results such as new biomarkers and clinical knowledge.

### 2.1 Longitudinal human data

#### a. Hypothesis-generating analyses of biological markers & environmental moderators

We will leverage harmonized data from a large set of human studies to examine the relationship between ELS and multi-morbidity across the lifespan, identify potential molecular markers and quantify the protective vs. exacerbating role of modifiable lifestyle factors. These datasets together span from pregnancy to old age, including the well-known Avon Longitudinal Study of Parents and Children (ALSPAC), Generation R Study (GenR), Northern Finland Birth Cohorts (NFBC), UK Biobank, Rotterdam Study, and the Netherlands Study of Depression and Anxiety (NESDA).

Note that other prominent birth cohorts exist outside of Europe, such as the well-known Dunedin Study [31], which may be considered for inclusion in later stages of the project if there is a need to increase the sample size. While the analyses in the child cohorts (e.g., Generation R, ALSPAC) will focus on life events and circumstances experienced in childhood (up to age 10), later life events and circumstances—experienced in adolescences and adulthood—will be taken into account in the adult cohort analysis (e.g., NFBC, Rotterdam Study, NESDA). In particular, we aim to assess how ELS associates with later PCM multimorbidity by:

adjusting for the continuity of life events (i.e., treating later adverse life events as covariates, allowing us to assess the direct and unique contribution of early exposure to life events);studying the mediating effect of later life events (i.e., treating later events as a continuum of earlier risk exposures). In these analyses, we are particularly interested in the mediating effects of educational attainment, own and parental socioeconomic position (including income), and substance (ab-)use, measured at a time when the study participants are in their teenage ages or later.

This will allow us to assess the degree to which early life events are unique risk factors for PCM multimorbidity or act through a continuum of risk exposures that starts in childhood but carries on into adulthood. Furthermore, we will make use of correlational multivariate analyses as well as novel latent modelling techniques to model the shared versus the unique contribution of ELS on multi-morbid outcomes (*Fig 3*). In these human studies, we will:

Define the relationship between ELS and multi-morbidity across the lifespan, by tracking risk factors of cardiovascular and metabolic disorders in children and adolescents, and the influence of early life stressors on tracking patterns, drawing a rich dataset of clinical samples and cohort studies publicly available or through members and collaborators of the consortium. We are currently seeking additional scientists and groups interested in collaborating with us;Identify candidate biological predictors and mediators of ELS effects on multi-morbidity (epigenetic marks, neuroendocrine function, inflammation, gut microbiome);Quantify the protective or exacerbating role of modifiable lifestyle factors and behaviours, which include exercise, diet, sleep, smoking and alcohol use in the relationships of ELS with biological markers and PCM multi-morbidity;Provide hypotheses and candidate biomarkers that can be used for causal inference and mediation studies, as well as in animal and in vitro studies;

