#### 2.3 Computational bioinformatics and machine learning methods

We plan to implement advanced bioinformatic, statistical and machine learning techniques to integrate and leverage the findings and determinants derived from human studies and experimental models. Several types of integration will take place:

Multi-omics integration of molecular interaction networks at different levels (DNA, RNA and proteins/metabolites) to dissect out the mechanistic chains across tissues;Structural equation modelling to model developmental timing and direction of associations, i.e. direct effects, as well as indirect pathways between variables and lifestyle factors affecting the pathways;Multi-cohort integration for bridging child/adolescent, adult and elderly cohorts and thus offer a life-course perspective on the link between ELS and multi-morbidity development;Machine learning models of multi-morbidity using unsupervised deep learning to simulate patient-specific trajectories towards multi-morbidity integrating identified biomarkers and pathways.

Subsequently, a proof-of-concept software will be assembled by integrating the predictive models within an existing e-health tool commercialised by COMBI; the Disease-State Fingerprint (DSF®). EarlyCause will extend it to account for multi-disease data and associations for the first time. The obtained tool will be pilot tested by COMBI’s usability experts to assess its acceptance and potential in future clinical management of multi-morbidities.

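### Adjusting for later adverse events, which the protocol also treats as mediators of early life stress, yields a direct effect only under conditions it does not state

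*Protocol article*

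**What the plan says.** Section 2.1a describes two ways of handling later events in the adult cohorts. The first is adjustment: "treating later adverse life events as covariates, allowing us to assess the direct and unique contribution of early exposure to life events". The second is mediation: "studying the mediating effect of later life events (i.e., treating later events as a continuum of earlier risk exposures". Within the second, the authors single out the "mediating effects of educational attainment, own and parental socioeconomic position (including income), and substance (ab-)use". All of these are to be taken from adolescence onwards, so after the early exposure.

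The conclusion to be drawn from both is also printed: "This will allow us to assess the degree to which early life events are unique risk factors for PCM multimorbidity", as opposed to acting through a chain of exposures that continues into adult life.

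Three other statements bear on the point. The section is headed as hypothesis-generating, and its aim is worded associationally: "we aim to assess how ELS associates with later PCM multimorbidity by". The Methods list on triangulation says the project will "Apply causal inference methods, including structural equation modelling, Mendelian randomisation, and molecular mediation". Section 2.3 adds "Structural equation modelling to model developmental timing and direction of associations, i.e. direct effects, as well as indirect pathways between variables". Neither of the last two is tied to the adjusted comparison in section 2.1a. The molecular mediation set out in section 2.1b concerns biological markers, not later life events.

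**The concern.** The article fixes both a method and the interpretation of its result. Later events are placed downstream of ELS in one item and conditioned on in the other, and the remaining ELS coefficient is read as a direct effect.

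Conditioning on later events links ELS to any other cause of those events. If such a cause also acts on PCM multi-morbidity and is not controlled, the ELS coefficient absorbs part of its effect. If the shared cause is itself a result of ELS, one regression cannot deliver the effect that bypasses later events. Leaving the cause out keeps the bias, and putting it in removes the part of the ELS effect that runs through it. Education, own socioeconomic position and substance use fit that description, since the article already treats them as lying between ELS and disease.

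What is at stake is the contrast between early stress as a risk in its own right and early stress as the start of a continuing chain. When all the paths are positive, the error pushes the answer towards the chain.

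**Working it through.** The document gives no effect size for any of these paths, so there is no figure to reproduce. **Every coefficient below is an assumption**, used only to show when the reading holds and how far it can fail.

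**1. Unmeasured shared cause not affected by ELS.** Let A be ELS, M later events, Y the outcome, and U a cause of both M and Y that is independent of A. A, M and U have unit variance. The paths are A→M = a, U→M = c, U→Y = g, a true direct effect A→Y = 0.20, and M→Y = 0.30. Regressing Y on A and M gives:

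- coefficient of A = 0.20 − a·c·g/(1 − a²)
- coefficient of M = 0.30 + c·g/(1 − a²)

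With a = c = g:

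- 0.2: A = 0.20 − 0.008/0.96 = 0.192; M = 0.30 + 0.04/0.96 = 0.342
- 0.3: A = 0.20 − 0.027/0.91 = 0.170; M = 0.30 + 0.09/0.91 = 0.399
- 0.4: A = 0.20 − 0.064/0.84 = 0.124; M = 0.30 + 0.16/0.84 = 0.490
- 0.5: A = 0.20 − 0.125/0.75 = 0.033; M = 0.30 + 0.25/0.75 = 0.633

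Simulation with one million records gave 0.190 for the first case and 0.124 for the third.

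**2. When there is no bias.** If a = 0, or if c or g is 0, the correction term vanishes and the coefficient of A is 0.20. So with a = 0.4 and no shared cause, adjustment recovers the direct effect exactly. It does not give the total effect, which is 0.20 + 0.4 × 0.30 = 0.32.

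**3. Direction.** If c and g have opposite signs, the error is upward: a = 0.4, c = 0.4, g = −0.4 gives 0.20 + 0.076 = 0.276.

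**4. Shared cause affected by ELS, and measured.** Let L = 0.4A + error, M = 0.3A + 0.4L + error, Y = 0.2A + 0.3M + 0.4L + error, with A and all errors of unit variance. The effect of A that does not pass through M is 0.2 + 0.4 × 0.4 = 0.36.

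- Adjusting for M only: regressing L on A and M gives 0.4/1.16 = 0.345 for M and 0.4 − 0.345 × (0.3 + 0.4 × 0.4) = 0.241 for A. The ELS coefficient is therefore 0.2 + 0.4 × 0.241 = 0.297.
- Adjusting for M and L: 0.20, because the 0.16 running through L is removed.
- Sequential g-estimation: regressing Y on A, M and L gives 0.30 for M. Regressing Y − 0.30M on A then gives 0.2 + 0.16 = 0.36.
- A linear path model gives the same: 0.20 + 0.4 × 0.4 = 0.36.

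**5. Ignored interaction.** Take binary A (30% exposed), M present in 50% of exposed and 25% of unexposed, and Y = 0.2A + 0.3M + 0.3AM + error. A model without the product term returned 0.32 in simulation. The controlled direct effect is 0.20 without later events and 0.50 with them. The natural direct effect is 0.2 + 0.3 × 0.25 = 0.275. One coefficient cannot stand for all three.

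**The case against.** The strongest reply has four parts.

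- **Status of the analysis.** The section is labelled hypothesis-generating and speaks of association. The unique-versus-chain question is not among the four human hypotheses in Table 2, and causal inference on ELS has its own section (2.1b). This lowers the weight. It does not remove the point, because a claim about direct and unique effects goes beyond association, and the results are meant to feed the causal, animal and cellular work.
- **Structural equation modelling is planned.** A path model can recover the right quantity, as step 4 shows. But the article does not link it to this comparison, and such a model also needs shared causes to be measured.
- **A condensed article.** Confounder lists, dating of events and the choice of estimator may fairly be left to a fuller plan, and their absence is no fault. The point rests only on the interpretation that the article itself prints.
- **What counts as direct.** If education, socioeconomic position and substance use belong to the set of later exposures, the effect that avoids all of them may be the one intended. In step 4 that is 0.20, and adjusting for both variables is then correct. This stands, and it is why the estimand has to be named.

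A reader might infer that the estimate must be biased because later events are consequences of ELS. Step 2 shows that this is not sufficient. A reader might also infer that some adjusted-for events follow the onset of disease. That is possible, but the text does not settle it.

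**Conclusion.** The concern holds in conditional form. The article attaches a direct-effect reading to adjustment for variables it also treats as mediators, and gives none of the conditions that reading needs. Its own list of mediators supplies plausible candidates for breaking them.

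The documents do not show that the estimate will be wrong, or by how much. With assumed positive paths of 0.2 to 0.5, a true 0.20 becomes 0.192 to 0.033, a shortfall of about 4% to 83%. With weak paths the error is negligible, and with mixed signs it reverses. It would be too strong to say that the analysis will hide a real early effect, or that no regression-based method can work. The point is of moderate severity: it affects the interpretation of one exploratory comparison and can be corrected on data the cohorts already hold.

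**What to change.** 1. Report the total ELS effect, adjusted for pre-exposure confounders only, beside the model that adjusts for later events.
2. State which direct effect is meant, for example the controlled direct effect not passing through later events. Say whether education, own socioeconomic position and substance use count as part of the later chain or as confounders of it. Allow for an interaction between ELS and later events.
3. Estimate that effect by sequential g-estimation, a marginal structural model or an equivalent path model, with measured ELS-affected confounders entering only at the later-event and outcome stage.
4. Add a sensitivity analysis for unmeasured causes shared by later events and outcome. The methods in item 3 do not cure these.
5. Where dates are available, count only later events that precede PCM onset.
6. If items 2 to 4 are not done, call the result an adjusted association and drop the wording about direct or unique effects.

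The cost is revised wording, some extra programming and slightly wider standard errors. No new data collection is needed.
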